## 9. Statistical Methods – Sensitivity analyses

A sensitivity analysis will estimate treatment effects on the primary outcome at 4 weeks assuming only patients who completed the treatment without major protocol violations at week 4. The sensitivity analysis will be based on t-tests for continuous variables and chi-squared tests for categorical variables

## 10. Missing data reporting and assumptions/statistical methods to handle missing data

Missing data will be handled with the multiple imputation with 20 iterations for the primary outcome. Baseline characteristics of patients who provided the primary outcome and those who did not will be compared using t tests or chi-square tests.

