#### 4. The Target Number of Participants and Estimation Basis

- (1) Estimation of the number of patients: The following is assumed using the reference literature of prior studies to estimate the number of patients.
- (2) Level of significance,  $\alpha_{\text{two-sides}} = 0.05$ .
- (3) Type 2 error ( $\beta$ ) is set to 0.2, and the power of the test is set to 80%.
- (4) Based on our pilot study and the previous studies about the minimal clinically important difference (MCID) [28, 29], we assumed that the primary outcome (a total WOMAC score at 4 weeks) in Tuina group was expected to have mean difference of 7 to mPT with a standard deviation for both groups of 13.
- (5) Compliance: 80% (the ratio expected to receive treatment 8 times or more during the 3-week treatment period).
- (6) Sample size calculation for the trial by using PASS 15 (Power Analysis and Sample Size Software (2017). NCSS, LLC. Kaysville, Utah, USA, [ncss.com/software/pass](http://ncss.com/software/pass).)

As a result of applying (1), (2), (3), (4), and effect size, the sample size is calculated to be 140 in total, 70 patients in each group.

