### **4. Level of statistical significance and Confidence intervals to be reported**

All applicable statistical tests will be 2-sided and will be performed using a 5% significance level. All confidence intervals will be 95% confidence intervals.

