### **5. Analysis Populations**

The primary analysis will be based on the principle of intention-to-treat (ITT), defined as all available data from all randomized patients were originally assigned, regardless of their adherence to their assigned treatments.

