### **7. Outcome Definitions**

**Primary Outcome** The change in the total Western Ontario and McMaster University Osteoarthritis Index (WOMAC) from baseline to 4 weeks

**Secondary Outcomes** The secondary outcomes covered pain, physical function, and patients' overall assessment of disease severity.

- **Pain Dimensions** WOMAC pain (the change between the baseline and 4, 8, and 16 weeks), the worst knee pain in the last 24 hour using NRS(the change between the baseline and 4, 8, and 16 weeks) ;

- **Function Dimensions** the average function of previous week using WOMAC function (the change between the baseline and 4, 8, and 16 weeks), WOMAC stiffness (the change between the baseline and 4, 8, and 16 weeks), 30 Second Time Chair Rise Test (the change between the baseline and week 4), Timed Up and Go Test Time (the change between the baseline and week 4), One Leg Standing Test (the change between the baseline and week 4);
- **Patients' overall assessment of disease severity:** the 12-item Short Form Health Survey (the change between the baseline and 4, 8, and 16 weeks), the patient global assessment (the change between 4, 8, and 16 weeks);
- **Criteria of Response Rate:** The OMERACT-OARSI responder criteria to assess the response rate of treatment for KOA at 4 weeks.
- **The blinding assessment**

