## 8. Analysis methods

We will use intention-to-treat analyses, analyses will be conducted by a statistician blinded to treatment allocation, with two-sided hypothesis tests. Changes from baseline will be presented for each group at each time point using the mean change and 95% confidence intervals.

**Primary outcome** Primary outcome will apply the repeated measures analysis of variance. Age, sex, BMI, baseline WOMAC score, medication as the covariates. The mean difference in change from baseline to 4 weeks of WOMAC total as the dependent variables, and group (Tuina group and mPT), time (baseline, week 4, 8 and 16), and the group  $\times$  time interaction as independent variables. The approximate normality and Mauchly's test of sphericity were examined. Then the interaction of group-interaction term was tested first. If significant, between-group differences at each time point were tested. If not significant, the treatment main effect was tested next.

**Secondary outcomes** For repeated measures of continuous outcome, including the subscale of WOMAC, NRS, SF-12 and PGA, will be estimated using the repeated measures analysis of variance, 30 Second Time Chair Rise Test, TUG and One Leg Standing Test will be applied with an independent t test for normal distribution, Mann-Whitney U test for unnormal distribution. And for categorical variables- responder criteria, will be compared across groups with the  $\chi^2$  tests or Fisher's exact test.

**Blinding outcome** Blinding assessment will apply the James blinding index with the blinding package of SAS software.

**Effect size** Effect size will be computed with mean group-difference/baseline SD; **MCID** The minimal clinically important difference (MCID) of WOMAC- total is set as 14%, which will be calculated with the change of baseline and the corresponding evaluation time point/baseline

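### Imputation is tied to the week-4 primary outcome, but the primary model also needs WOMAC total at weeks 8 and 16, so the ITT analysis may become a four-visit complete-case analysis

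*Supplement*

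**What the plan says.** Four parts of the SAP (Additional file 4) bear on who enters the primary analysis.

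- Section 5 defines the ITT analysis as "all available data from all randomized patients were originally assigned", whatever their adherence.
- Section 7 defines the primary outcome as "The change in the total Western Ontario and McMaster University Osteoarthritis Index (WOMAC) from baseline to 4 weeks". The note to Additional file 5 uses the term in the same way: the 13 patients counted as missing the primary outcome (7 Tuina, 6 mPT) are those without WOMAC total at week 4.
- Section 8 analyses the primary outcome by repeated measures ANOVA, with group, "time (baseline, week 4, 8 and 16") and their interaction as factors, covariates that include baseline WOMAC, and Mauchly's test of sphericity. Section 11 names SPSS as the main software.
- Section 10 gives the only missing-data rule: "Missing data will be handled with the multiple imputation with 20 iterations for the primary outcome".

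No section says what happens when WOMAC is missing at week 8 or week 16.

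**The concern.** The imputation and the model do not cover the same set of values. A classical repeated measures ANOVA, the kind that Mauchly's test belongs to, needs a complete vector of scores for each patient. If only week 4 is filled in, two groups can still be lost:

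- patients who left before week 4 and did not return, for whom the imputed week-4 value is never used;
- patients whose week-4 score was observed but who missed week 8 or 16, who leave an analysis whose target is week 4.

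What is at stake is the ITT claim. The primary comparison could rest on patients selected by their attendance after the primary time point. If the 13 did not return, it could even hold fewer patients than the week-4 per-protocol table in Additional file 6 (63 + 64 = 127).

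**Working it through.** **Inputs.** Two-sided 5% level (SAP section 4). From the protocol's section on the target number of participants: type 2 error "is set to 0.2, and the power of the test is set to 80" per cent, difference and SD "expected to have mean difference of 7 to mPT with a standard deviation for both groups of 13", and "Compliance: 80% (the ratio expected to receive treatment 8 times or more during the 3-week treatment period"). Missing at week 4: 13 of 140 (Additional file 5). Loss at weeks 8 and 16 is not given; 0–20% of the 127 patients with a week-4 score is assumed.

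**1. The plan's own figure.** Normal formula: n per arm = 2(1.960 + 0.842)² × 13² / 7² = 54.1, so 55. The t test needs 56. With the 20% allowance, 56 / 0.8 = 70 per arm, or 140 in total. The stated size reproduces, but only with the allowance (without it, 2 × 56 = 112).

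**2. What week-4 imputation restores.**

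| Patient | Week 4 | Weeks 8 and 16 | In the four-visit ANOVA? |
|---|---|---|---|
| Missed week 4, did not return | imputed | missing | no |
| Missed week 4, attended both later visits | imputed | observed | yes |
| Attended week 4, missed a later visit | observed | one or both missing | no |
| Attended all visits | observed | observed | yes |

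Imputation changes the outcome only in the second row. The documents do not say how many of the 13 are in that row.

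**3. Patients kept and power.** Assume that none of the 13 returned, so patients kept = 127 × (1 − later loss). Power is for 7 points, first with SD 13, then with the residual SD after baseline adjustment, 13 × √(1 − r²). With r = 0.5 that is 13 × √0.75 = 11.26.

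This r agrees with Additional file 6. The SD of change is the CI half-width divided by t, times √n: 2.68 / 1.999 × √63 = 10.64 for Tuina and 3.72 / 1.998 × √64 = 14.90 for mPT. Then r = (SD₀² + SD₄² − SD of change²) / (2 × SD₀ × SD₄):

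- Tuina: (182.8 + 155.3 − 113.2) / 336.9 = 0.67
- mPT: (185.5 + 161.3 − 221.9) / 345.9 = 0.36
- average: about 0.51

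| Later loss among the 127 | Kept | Excluded of 140 | Power, SD 13 | Power, baseline-adjusted |
|---|---|---|---|---|
| 0% | 127 | 9% | 0.853 | 0.935 |
| 5% | 121 | 14% | 0.835 | 0.923 |
| 10% | 114 | 18% | 0.814 | 0.909 |
| 15% | 108 | 23% | 0.792 | 0.893 |
| 20% | 102 | 27% | 0.767 | 0.874 |

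With all 140 the two figures are 0.886 and 0.955.

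**4. Bias.** Simulation (6,000 runs): 70 per arm, SD 13, r = 0.5, no true difference, all week-4 scores observed, then patients with a later missed visit removed. The estimate is the baseline-adjusted week-4 difference; its Monte Carlo error is about 0.03.

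| Later loss | Same dependence on week-4 score in both arms (log-odds 1 per SD) | Log-odds 1 per SD in one arm, random in the other | Log-odds 0.5 per SD in one arm, random in the other |
|---|---|---|---|
| 10% | 0.0 | −0.9 | −0.5 |
| 15% | 0.0 | −1.3 | −0.8 |
| 20% | 0.0 | −1.7 | −1.0 |

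Keeping every week-4 score gives about 0 throughout. In the first two scenarios the SE rises by about 3–7% and 4–10%.

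**The case against.** **The phrase can be read more widely.** Section 10 does not say week 4 only. Section 8 sets out a four-visit model of WOMAC total under its primary-outcome label, and section 5 promises all randomised patients. An analyst could reasonably impute every visit, and then nobody is lost. This stands as a possible reading, so the exclusion is a risk and not a certainty. It does not settle the matter, because section 7 and Additional file 5 both fix the term at week 4.

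**Listwise deletion is inferred.** No section states it. The inference is sound for the named method, but it shows a conflict between sections and not a declared exclusion.

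**Part of the fault lies in the model.** Section 8 names the change to week 4 as the dependent variable and also uses a four-level time factor that includes baseline. Which visits the model needs is therefore itself unclear. That is a reason to mend sections 8 and 10 together.

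**Stronger readings that do not hold.**

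- A reader might infer from the unadjusted column that power falls below 80%. The planned model adjusts for baseline WOMAC, and with r = 0.5 power stays at 0.87 or more even at 20% later loss. The sample size also already carries a 20% allowance.
- A reader might expect the SE to rise by 6–14%. The scenarios above with log-odds 1 per SD give about 3–10%.
- A reader might take 0.9–1.7 points as the expected bias. It needs loss that follows the week-4 score in one arm and is random in the other. The documents give no evidence of that, and week-4 loss was nearly equal (7 and 6).

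**Conclusion.** The point holds as a mismatch between sections 5, 7, 8 and 10. Followed by the SAP's own definition of the primary outcome, the primary ITT analysis may become a complete-case analysis over four visits. Any of the 13 patients (9.3% of 140) who also lack week 8 or 16 would stay out despite imputation, and patients with an observed week-4 score could be dropped.

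The size cannot be fixed from the documents. It rests on the unreported later losses, on how many of the 13 returned, and on classical ANOVA being used as named. Bias in the week-4 difference runs from about 0 (same loss mechanism in both arms) to about 0.9–1.7 points, or 13–24% of the 7-point target, in the one-arm scenario at 10–20% loss. The case for change rests on the ITT conflict and on possible selection bias, not on power or precision. The SAP should be changed, because who enters the primary analysis should not depend on how one phrase is read.

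**What to change.** Either of two changes is enough.

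- **Joint imputation.** State in section 10 that WOMAC total at weeks 4, 8 and 16 is multiply imputed jointly, by arm, for all 140 randomised patients. Use the baseline covariates (baseline WOMAC, age, sex, BMI) as predictors. Give the number of imputed data sets, for example 20, because a count of iterations does not clearly say this.
- **Mixed model.** Replace the repeated measures ANOVA for the primary outcome in section 8 with a likelihood-based mixed model that uses every observed visit, with the week-4 contrast as the primary estimate.

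In both cases add that no patient with an observed week-4 WOMAC total leaves the primary analysis because of a later missed visit.

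The cost is a few lines of SAP text and slightly more programming. No new data are needed.

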## 11. Statistical Software

SPSS 24.0 (SPSS Inc.) will be mainly used for calculations in this study.

### Additional file 5 - Baseline Characteristics and Outcome Scores of Participants Who Did and Did Not Complete Primary Outcome

| Characteristics                                   | Missing
primary outcome
(n =13) a | Provided
primary outcome
(n=127) b | P
value |
|---------------------------------------------------|----------------------------------------------------|-----------------------------------------------------|-------------------|
| Age, mean (SD), years                             | 57.38 (9.2)                                        | 60.35 (7.77)                                        | 0.199             |
| Female, No. (%)                                   | 13 (100.00%)                                       | 96 (88.07%)                                         | 0.095             |
| BMI, mean (SD), kg/m                  | 24.35 (2.24)                                       | 25.09 (3.05)                                        |                   |
| Race, n (%)                                       |                                                    |                                                     |                   |
| Han                                               | 10 (76.92%)                                        | 122 (96.06%)                                        | 0.027             |
| Minorities                                        | 3 (23.08%)                                         | 5 (3.93%)                                           |                   |
| Duration, Median (IQR), Months                    | 41.00 (9.50,114.50)                                | 44.00 (10.75,109.75)                                | 0.691             |
| Kellgren criteria, No. (%)                        |                                                    |                                                     |                   |
| Kellgren II                                       | 6 (46.15%)                                         | 71 (55.90%)                                         | 0.50              |
| Kellgren III                                      | 7 (53.84%)                                         | 56 (44.09%)                                         |                   |
| Concomitant disease, No. (%)                      |                                                    |                                                     |                   |
| 0                                                 | 7 (53.85%)                                         | 54 (42.52%)                                         | 0.540             |
| 1                                                 | 5 (38.46%)                                         | 41 (32.28%)                                         |                   |
| 2                                                 | 1 (7.69%)                                          | 23 (18.11%)                                         |                   |
| ≥3                                                | 0 (0%)                                             | 9 (7.09%)                                           |                   |
| Education, No. (%)                                |                                                    |                                                     |                   |
| High school or less                               | 12 (92.30%)                                        | 82 (64.57%)                                         | 0.124             |
| College                                           | 1 (7.69%)                                          | 36 (28.35%)                                         |                   |
| Advanced degree                                   | 0 (0%)                                             | 9 (7.09%)                                           |                   |
| Working status, No. (%)                           |                                                    |                                                     |                   |
| Employed                                          | 5 (38.46%)                                         | 65 (51.18%)                                         | 0.339             |
| Retired                                           | 8 (61.54%)                                         | 54 (42.52%)                                         |                   |
| Others                                            | 0 (0%)                                             | 8 (6.30%)                                           |                   |
| Marital status, No. (%)                           |                                                    |                                                     |                   |
| Married                                           | 10 (76.92%)                                        | 117 (92.12%)                                        | 0.194             |
| History of treatment, No. (%)                     |                                                    |                                                     |                   |
| Pharmaceuticals                                   | 11 (84.62%)                                        | 108 (85.04%)                                        | 1.000             |
| Intervention therapy                              | 5 (38.46%)                                         | 66 (51.97%)                                         | 0.353             |
| Physiotherapy                                     | 6 (46.15%)                                         | 76 (59.84%)                                         | 0.340             |
| Others                                            | 0 (0%)                                             | 10 (7.88%)                                          | 0.628             |
| The Satisfaction of Previous Treatment, mean (SD) | 5.50 (1.99)                                        | 5.25 (2.00)                                         | 0.533             |
| WOMAC, mean (SD)                                  |                                                    |                                                     |                   |
| Total                                             | 18.85 (11.34)                                      | 19.26 (13.51)                                       | 0.915             |
| Pain subscale                                     | 4.15 (2.38)                                        | 4.57 (2.88)                                         | 0.619             |
| Stiffness subscale                                | 1.31 (1.44)                                        | 1.57 (1.74)                                         | 0.605             |
| Function subscale                                 | 13.38 (8.39)                                       | 13.13 (10.06)                                       | 0.929             |
| NRS, mean (SD)                                    | 5.50 (1.43)                                        | 5.90 (1.55)                                         | 0.378             |

|                                                         |                    |                   |       |
|---------------------------------------------------------|--------------------|-------------------|-------|
| SF-12, mean (SD)                                 |                    |                   |       |
| Physical health                                         | 37.41 (8.34)       | 37.85 (7.55)      | 0.746 |
| Mental health                                           | 48.23 (10.02)      | 51.39 (9.41)      | 0.057 |
| 30 Second Time Chair Rise Test, mean (SD), times | 10.08 (3.98)       | 10.96 (3.62)      | 0.667 |
| Timed Up and Go Test Time, mean (SD), second     | 11.24 (1.84)       | 11.30 (2.96)      | 0.906 |
| One Leg Standing Test, mean (SD), second         | 21.95 (11.36)      | 18.76 (10.63)     | 0.928 |
| Target knees, No. (%)                            |                    |                   |       |
| Left                                                    | 6 (46.15%)         | 60 (47.24%)       | 0.940 |
| Right                                                   | 7 (53.85%)         | 67 (52.76%)       |       |
| Credibility/Expectancy Questionnaire, mean (SD)  |                    |                   |       |
| Credibility questionnaire                               | -0.17 (-0.70,0.47) | 0.28 (-0.40,0.74) | 0.20  |
| Expectancy questionnaire                                | 0.59 (-0.79,0.72)  | 0.13 (-0.78,0.58) | 0.96  |

**Note:** a: Seven patients in the Tuina group, 6 in the mPT group, did not complete the primary outcome – WOMAC-total at week 4. b: 63 patients in the Tuina group, 64 in the mPT group, complete the primary outcome – WOMAC-total at week 4. *p*-values based on t-tests for continuous characteristics and chi-squared tests for categorical characteristics.

**Additional file 6 - WOMAC-total and Sub-Domain Scores, Differences Between Groups, at week 4 (Per Protocol set)**

| Outcomes                           | Tuina
(n=63) | mPT
(n=64) | Between-group comparison
Mean difference (95% CI) | P value |
|-------------------------------------------|-------------------------|-----------------------|--------------------------------------------------------------|----------------|
| Primary outcome                    |                         |                       |                                                              |                |
| WOMAC-Total, mean (SD)             |                         |                       |                                                              |                |
| Baseline                                  | 19.10 (13.52)           | 19.42 (13.62)         | -0.33 (-5.09, 4.44)                                          | 0.892          |
| Week 4                                    | 13.44 (12.46)           | 13.58 (12.70)         | -0.13 (-4.55, 4.29)                                          | 0.952          |
| Mean change from baseline-week 4 (95% CI) | -5.65 (-8.33, -2.97)    | -5.84 (-9.56, -2.12)  | 0.19 (-4.36, 4.74)                                           | 0.933          |
| WOMAC-Pain, mean (SD)              |                         |                       |                                                              |                |
| Baseline                                  | 4.49 (2.80)             | 4.64 (2.98)           | -0.15 (-1.17, 0.87)                                          | 0.773          |
| Week 4                                    | 2.75 (2.38)             | 3.06 (2.62)           | -0.32 (-1.20, 0.56)                                          | 0.478          |
| Mean change from baseline-week 4 (95% CI) | -1.75 (-2.44, -1.05)    | -1.58 (-2.37, -0.78)  | -0.17 (-1.21, 0.88)                                          | 0.751          |
| WOMAC-Stiffness, mean (SD)         |                         |                       |                                                              |                |
| Baseline                                  | 1.71 (1.88)             | 1.42 (1.60)           | 0.29 (-0.32, 0.91)                                           | 0.347          |
| Week 4                                    | 1.37 (1.61)             | 1.12 (1.44)           | 0.24 (-0.30, 0.78)                                           | 0.377          |
| Mean change from baseline-week 4 (95% CI) | -0.35 (-0.71, 0.01)     | -0.30 (-0.71, 0.12)   | -0.05 (-0.60, 0.49)                                          | 0.850          |
| WOMAC-Function, mean (SD)          |                         |                       |                                                              |                |
| Baseline                                  | 12.89 (10.00)           | 13.36 (10.19)         | -0.47 (-4.02, -3.08)                                         | 0.793          |
| Week 4                                    | 9.30 (9.32)             | 9.39 (9.37)           | -0.09 (-3.37, 3.19)                                          | 0.957          |
| Mean change from baseline-week 4 (95% CI) | -3.59 (-5.54, -1.64)    | -3.97 (-6.74, -1.19)  | 0.38 (-2.99, 3.75)                                           | 0.823          |

